## Abstract

**Background:**

The most common intestinal operation in Crohn’s disease (CD) is an ileocolic resection. Despite optimal surgical and medical management, recurrent disease after surgery is common. Different types of anastomoses with respect to configuration and construction can be made after resection for example, handsewn (end-to-end and Kono-S) and stapled (side-to-side). The various types of anastomoses might affect endoscopic recurrence and its assessment, the functional outcome, and costs. The objective of the present study is to compare the three types of anastomoses with respect to endoscopic recurrence at 6 months, gastrointestinal function, and health care consumption.

**Methods:**

This is a randomized controlled multicentre superiority trial, allocating patients either to side-to-side stapled anastomosis as advised in current guidelines or a handsewn anastomoses (an end-to-end or Kono-S). It is hypothesized that handsewn anastomoses do better than stapled, and end-to-end perform better than the saccular Kono-S. Two international studies with a similar setup will be conducted mainly in the Netherlands (End2End) and Italy (HAND2END). Patients diagnosed with CD, aged over 16 years in the Netherlands and 18 years in Italy requiring (re)resection of the (neo)terminal ileum are eligible. The first part of the study compares the two handsewn anastomoses with the stapled anastomosis. To detect a clinically relevant difference of 25% in endoscopic recurrence, a total of 165 patients will be needed in the Netherlands and 189 patients in Italy. Primary outcome is postoperative endoscopic recurrence (defined as Rutgeerts score ≥ i2b) at 6 months. Secondary outcomes are postoperative morbidity, gastrointestinal function, quality of life (QoL) and costs.

**Discussion:**

The research question addresses a knowledge gap within the general practice elucidating which type of anastomosis is superior in terms of endoscopic and clinical recurrence, functionality, QoL and health care consumption. The results of the proposed study might change current practice in contrast to what is advised by the guidelines.

**Trial registration:**

NCT05246917 for HAND2END and NCT05578235 for End2End (http://www.clinicaltrials.gov/).

**Supplementary Information:**

The online version contains supplementary material available at 10.1186/s12893-024-02340-3.

## Background

Crohn’s disease (CD) is a chronic inflammatory disease of the gastrointestinal tract with an unknown etiology and cure. The often transmural inflammation may be refractory to anti-inflammatory medication and can be complicated by fistula formation and strictures. Despite improvements in medical management, complicated disease leads to surgery in one-third of the patients requiring major abdominal surgery within 5 years of their diagnosis and up to 60% of patients need surgery during their disease course [1–6]. The L!RIC study demonstrated that upfront surgical management of uncomplicated ileocecal disease results in a quality of life at 1 year that is at least as good as or better than biological maintenance therapy. Surgery has been shown to be more cost-effective and associated with a lower rate of re-resection and biological use at the 5-year follow-up compared to biological maintenance therapy [7, 8].

Nonetheless, a recent prospective study by the REMIND group, reported clinical recurrence rates to be as high as 36% at 3 years and 60% at 5 years, and endoscopic recurrence (modified Rutgeerts score ≥ i2b) is reported to be as high as 70% at 1 year [9, 10].

Healthcare professionals in the field of IBD, have given considerable attention to the technical aspects of ileocolic resection with the aim of reducing recurrent Crohn’s disease after surgery. A potential role of the mesentery was highlighted, emphasizing the involvement of memory T-cells in lymphatic mesenteric tissue in perpetuating the disease at anastomosis and neo-terminal ileum [11]. Preliminary results from the SPICY trial showed that extended mesenterectomy as opposed to mesenteric sparing in ileocolic resection, does not reduce endoscopic recurrence as assessed by central reading at 6 months [12].

In a retrospective cohort study, a newly introduced anastomosis, the Kono-S, appeared to be associated with less endoscopic recurrence than the stapled side-to-side anastomosis [13]. Although the study results were notably flawed, the study reignited interest in the various types of anastomoses and their impact on disease recurrence. However, a recent prospective study demonstrated no difference in endoscopic recurrence between Kono-S and stapled side-to-side anastomosis, (47.5% vs 44.3%, respectively; *p* = 0.674), illustrating the controversies in the current literature [14].

The currently recommended anastomosis after ileocolic resection is the stapled side-to-side anastomosis due to its ease of construction and safety [15, 16]. The third type of anastomosis, the end-to-end handsewn anastomosis appears to be less popular due to its technical complexity [17]. However, a recent study comparing handsewn end-to-end with stapled side-to-side anastomosis, showed reduced healthcare consumption in favour of the end-to-end anastomosis [18]. Additionally, the authors found no difference in endoscopic recurrence rates at 2 years postoperatively (25.4% vs 39.3%, respectively; *p* = 0.112). In terms of functionality, the end-to-end anastomosis theoretically outperforms the Kono-S and stapled side-to-side anastomosis. Both have a saccular design that is presumed to be associated with luminal content stasis and consequently functional problems and recurrent Crohn’s disease [19, 20]. To date, prospective data from a randomized controlled trial comparing these three anastomoses are lacking, and it remains unclear which anastomotic technique is superior in terms of endoscopic recurrence. The aim of these two multicentre international randomized studies is to determine which anastomoses handsewn (end-to-end versus Kono-S anastomosis) or side-to-side stapled anastomosis after ileocolic resection for Crohn’s disease is superior with respect to endoscopic recurrence, gastrointestinal function, and (healthcare) costs.

## Methods/design

This study protocol is written in accordance with the SPIRIT guidelines [21, 22]. The SPIRIT checklist is provided in a supplementary file 1.

### Objectives

The primary objective of these two multicentre international randomized studies is to determine which anastomosis, handsewn (end-to-end versus Kono-S anastomosis) or side-to-side stapled anastomosis after ileocolic resection for Crohn’s disease is superior with respect to endoscopic recurrence. Secondary objectives include evaluating gastrointestinal function, postoperative morbidity, quality of life and costs.

### Study design

The HAND2END and End2End studies are two separate studies with similar designs conducted respectively in both Italy and the Netherlands. Three Italian centres and 12 centres in the Netherlands will participate in this prospective study. Both studies are multicentre randomized controlled superiority trials consisting of two phases. In phase one the two handsewn anastomoses (Kono-S and end-to-end) will be compared with the side-to-side stapled anastomosis. In this phase, participants will be randomized in a 2:1 ratio between (1) handsewn end-to-end (Fig. 1) or Kono-S anastomosis (Fig. 2) and (2) stapled side-to-side anastomosis (Fig. 3). If the interim analysis shows superiority of the handsewn anastomosis, phase two of the trial will compare the end-to-end (Fig. 1) with the Kono-S anastomosis (Fig. 2). In the Netherlands, three academic and eight non-academic teaching hospitals have agreed to participate in this national initiative. This multicentre (international) collaborative will greatly facilitate the (inter)national implementation of the study results. The attached video clips will demonstrate one way of performing these anastomoses (Supplementary files 2, 3, 4).

**Fig. 1 Fig1:**
[figure not shown]
Handsewn end-to-end anastomosis

**Fig. 2 Fig2:**
[figure not shown]
Handsewn Kono-S anastomosis

**Fig. 3 Fig3:**
[figure not shown]
Stapled side to side anastomosis

### Study population

All patients diagnosed with CD undergoing primary ileocolic resection or resection of recurrent disease of the neoterminal ileum will be considered for inclusion. To be eligible, a subject must meet all of the following criteria: adults of either sex, age ≥ 16 years or ≥ 18 years (in the Netherlands or Italy, respectively), diagnosed with either disease of the (neo)terminal ileum or ileocolic disease (L1 and L3 disease), previously confirmed by endoscopy with an indication for resection. Patients need to have a recent update of imaging (for example, ultrasound, MR/CT enterography) before surgery, the clinical case should have been discussed at the local multidisciplinary meeting and patients need to be able to comply with the study protocol and provide written informed consent. A potential subject who meets any of the following criteria will be excluded from participation in this study: inability to provide informed consent, patient under the age of 16 or 18 years (in the Netherlands or Italy, respectively), clinically significant medical condition within 6 months before the operation (for example, myocardial infarction, active angina, congestive heart failure, or other condition that would, in the opinion of the investigators, compromise patient’s safety), history of cancer of less than 5 years that might influence the patient’s prognosis, emergent operation, pregnancy or breastfeeding.

### Ethical considerations

The trials will be conducted according to Good Clinical Practice guidelines and the principles of the Declaration of Helsinki (2013). The End2End study was approved by the Medical Ethical Committee of the Amsterdam UMC, Amsterdam (MEC 2022.0533). The protocol is registered by the Dutch Central Committee on Research Involving Human Subjects (NL81981.018.22). The HAND2END study was approved by the Medical Ethical Committee of the IRCCS San Raffaele, Milan (EC-13/06/2022, version 2.0).

### Informed consent procedure

All eligible patients referred for outpatient consultation for surgical resection will be screened for inclusion criteria during outpatient clinic visits. Patients who meet all the inclusion criteria will be informed on the details of the study and the possibility of participating in the trial. The informed consent procedure includes explanation of the study, the provision of a patient information sheet and ample time for addressing questions before signing the study consent form prior to the surgical procedure. Written informed consent is obtained by a participating surgeon, resident or trained research nurse before any study procedures. All included patients will be registered in Castor EDC and will be assigned a six-digit study number. A log of the assigned subject number will be maintained by each study site.

### Randomization

Randomization of consented study participants to either handsewn (end-to-end or Kono-S) or stapled side-to-side anastomosis will be done using an online-based system for allocation concealment (Castor EDC). Allocation concealment will be ensured, as the service will not release the randomization code until the patient has signed for informed consent and has been recruited into the trial. Randomization will be stratified for primary or repeated ileocolic resection. The randomization block sizes will not be disclosed, to ensure concealment. There is no blinding of treatment allocation for the treating surgeon. The treatment will be blinded for all other physicians (for example, gastroenterologists, central readers) and patients. A statistician blinded to treatment allocation will analyse the data.

### Study outline

#### Preoperative

Adult patients with ileocolic Crohn’s disease (CD) or recurrent disease of the terminal ileum will be screened during outpatient clinic visits. Qualified subjects expressing interest will be offered participation in the trial following multidisciplinary team discussion and will sign a written consent form if they agree to be enrolled. Medical treatment will be advised to be discontinued before surgery: glucocorticoids will be weaned to < 20 mg per day, and biologic agents and immunomodulators will be stopped at time of surgery. Prior to surgery, all patients must have had a colonoscopy with biopsy to confirm disease of the (neo)terminal ileum, and a recent update of imaging (for example ultrasound, MR or CT enterography). Baseline characteristics will be collected. Patients will all be treated in an enhanced recovery protocol.

#### Surgery

At the time of surgery, all the procedures will be initiated as a laparoscopic procedure with conversion to an open operation only if clinically indicated. Close bowel ileocolic resection is advised to preserve vascularization.

Group I: End-to-end handsewn or Kono-S anastomose. The end-to-end anastomosis is fashioned either by enlarging the small bowel diameter with an antimesenteric incision to fit the large bowel lumen or by tailored resection of a part of the staple line of the cross stapled colon. The Kono-S anastomosis is made according to the description by Kono [23]. The length of the actual anastomosis should be approximately 7 cm (Figs. 1, 2, video).

Group II: The side-to-side anastomosis is done according to local practice using a linear stapler either anisoperistaltic or isoperistaltic.

The rest of the operation will be identical. Care should be taken to ensure that, as a routine, the colon is anastomosed just beyond the ileocolic angle. Operative, postoperative and pathology data will be collected.

#### Quality control of surgical procedure

To ensure that the surgical technique is performed correctly in all centres, quality control will be conducted. A video vignette of the surgical procedure will be shared with all participating centres as an example (video). Furthermore, the participating centres will be asked to provide photos of the anastomoses and the resected specimen. Finally, each centre will provide videos of the procedure when requested.

#### Postoperative

##### Postoperative morbidity

Data on postoperative morbidity will be collected. All adverse events (AEs) and severe adverse events (SAEs) will be documented throughout the hospital stay and outpatient visits.

##### Assessment of primary endpoint (endoscopic recurrence)

All patients will undergo endoscopy with biopsies taken from the distal ileum and proximal colon on either side of the anastomosis to assess endoscopic and histologic recurrence at 6 months after surgery. Endoscopic results will be classified according to the SES-CD subdivided according to location and the (modified) Rutgeerts scoring system [24]. All colonoscopies must be video recorded according to a standard operational procedure (video). The quality of endoscopic scoring and over scoring will be assessed comparing the scoring of the local gastroenterologist with that of the central reading panel.

After endoscopic assessment at 6 months, medication can be initiated according to the severity of endoscopic recurrence according to the guidelines and the treating physician’s preference.

##### Assessment of clinical recurrence, quality of life and health care consumption

The Crohn’s Disease Activity Index (CDAI) is determined at baseline and at 6 and 12 months postoperatively based on seven-days scoring by the patient before to these visits. Quality of life questionnaires are administered at each visit (preoperative, postoperative at 3 months, at 6 months and 12 months: the EuroQol, (EQ-5D-5L), 36-Item Short Form Health Survey (SF-36), and Inflammatory Bowel Disease Questionnaire (IBDQ). All types of healthcare consumption within the first year will be recorded, including readmission, emergency room visits, examinations, medical therapy etc.

##### Medical management

Patients will be treated according to the ECCO guidelines with respect to prophylactic medication after surgery.

##### Assessment of surgical recurrence

Patients will be followed up for up to 5 years after surgery to determine the reoperation rate for recurrent disease at the anastomotic site.

### Primary and secondary outcomes

The primary outcome is endoscopic recurrence at 6 months following ileocolic resection, defined as Rutgeerts score ≥ i2b assessed by local and central reading separately and blinded for the type of anastomosis. The quality of endoscopic scoring and over scoring will be assessed comparing the local scoring by the treating gastroenterologist with the central reading scoring for the different types of anastomosis.

Secondary outcomes include postoperative morbidity, the 6 months histologic and clinical recurrence rate and the need of restarting immunosuppressive medication within the first year postoperatively for endoscopic or clinical recurrence. For long term results, patient will be followed for at least 5 years to determine reoperation rate for recurrent disease at the anastomotic site. Additionally, quality of life will be measured with IBDQ, EQ-5D and SF- 36 together with health care consumption and costs.

### Sample size calculation

The primary endpoint is the post-operative endoscopic recurrence of Crohn’s disease at 6 months.

The study is powered to detect a clinically relevant difference of 25% endoscopic recurrence at 6 months between the two randomized surgeries, 50% versus 25%. Assuming a test with continuity correction with 90% power, and an two-sided alpha-level of 0.05, in 2:1 ratio a total of 63 patients in each surgical arm will be required, for a total enrolment of 189 patients including an anticipated dropout of 10% in the Italian HAND2END study. In the Dutch End2End study, assuming a test with continuity correction with 80% power, and a two-sided alpha-level of 0.05, in 2:1 ratio a total of 55 patients per arm will be required, for a total enrolment of 165 patients, allowing for a 10% dropout.

After enrolling 189 patients in Italy, requiring 2.5 years with a 0.5-year follow-up, or 165 patients in the Netherlands, requiring 2 years with a 0.5-year follow-up, an interim analysis is done to determine whether the handsewn anastomoses are superior to stapled side-to-side anastomosis. If the interim analysis shows superiority of the handsewn anastomosis, the trial will continue with the end-to-end and the Kono-S anastomosis only. To find a reduction in endoscopic recurrence from 28 to 13% within the two handsewn groups (end-to-end and Kono-S), an additional 88 patients need to be included, for a total of 277 in the HAND2END. In Italy, a total 189 or 277 patients will be required over 3 or 4 years.. In the Dutch study, another 71 patients per group need to be included, leading to a total of 307 patients. In the End2End study, a total of 165 or 307 patients are needed over 2.5 or 4 years. If no superiority within the handsewn anastomosis is expected from the interim analysis, the study will be stopped after inclusion of either 189 patients in Italy or 165 patients in the Netherlands, plus those that are already included in the period needed to reach the 0.5-year follow-up.

The Dutch sample size has been adjusted according to the ZonMW first-round review committee’s preference, explaining why the the Dutch numbers are slightly different from those in the Italian study.

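### The Italian enrolment of 189 cannot hold both the stated continuity correction and the stated 10% dropout; on the plan's own assumptions its power is about 87%, not 90%

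*Protocol article*

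**What the plan says.** The section "Sample size calculation" of the protocol article plans for a "difference of 25% endoscopic recurrence at 6 months between the two randomized surgeries, 50% versus 25" per cent. For the Italian trial it sets the test and the power: "Assuming a test with continuity correction with 90% power", with "an two-sided alpha-level of 0.05, in 2:1 ratio a total of 63 patients in each surgical arm will be required". The result is given as "63 patients in each surgical arm will be required, for a total enrolment of 189 patients including an anticipated dropout of 10" per cent.

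The Dutch End2End trial follows with the same rates, level, allocation and test, but at 80% power: "a total of 55 patients per arm will be required, for a total enrolment of 165 patients, allowing for a 10% dropout".

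The section "Study design" fixes the allocation: "participants will be randomized in a 2:1 ratio between (1) handsewn end-to-end (Fig. 1) or Kono-S anastomosis (Fig. 2) and (2) stapled side-to-side anastomosis". The figure per arm therefore refers to each of three surgical techniques, two of them handsewn: 63 stapled and 126 handsewn in Italy, 55 and 110 in the Netherlands. The Methods part of the abstract repeats both totals: "a total of 165 patients will be needed in the Netherlands and 189 patients in Italy".

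**The concern.** Both trials are described as allowing for a continuity correction and for 10% dropout. The Dutch total can be rebuilt with both. The Italian total equals the continuity-corrected requirement with no allowance for loss.

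If that is so, the first and decisive comparison in Italy, handsewn against stapled, has less than its stated 90% power once the anticipated dropout occurs. That comparison also decides whether the second phase opens. A reader would not notice the discrepancy, because the section attributes the difference between the two countries' numbers to a funding committee's preference and not to a different treatment of dropout.

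**Working it through.** **Inputs** (sections "Sample size calculation" and "Study design"): p1 = 0.50, p2 = 0.25, d = 0.25; k = 2 handsewn per stapled patient; two-sided alpha 0.05 (z = 1.960); power 90% (z = 1.2816) in Italy and 80% (z = 0.8416) in the Netherlands; dropout 10%. The article does not say which arm has the 50%. I assume the stapled arm, in line with the hypothesis.

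**Formulas.** With p̄ = (p1 + k·p2)/(1 + k) = 1/3, the stapled arm needs

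- uncorrected: n = [z_α·√((1 + 1/k)·p̄(1 − p̄)) + z_β·√(p1(1 − p1) + p2(1 − p2)/k)]² / d²
- corrected: n_c = (n/4)·[1 + √(1 + 2(1 + 1/k)/(n·d))]²

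**Dutch figure first, as a check on the method (80% power).**

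- n = (1.1316 + 0.4934)²/0.0625 = 42.25
- n_c = (42.25/4)·(1 + √1.2840)² = 48.06, so 49 evaluable per technique
- 49/0.9 = 54.4, so 55; 55 × 3 = 165

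This is the stated figure, with both the correction and the dropout in it. It confirms the formula, the reading of the arms and the dropout convention.

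**Italian figure (90% power).**

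- n = (1.1316 + 0.7514)²/0.0625 = 56.73
- n_c = (56.73/4)·(1 + √1.2115)² = 62.58, so 63 evaluable per technique
- 63 × 3 = 189 evaluable
- 63/0.9 = 70; 70 × 3 = 210 enrolled

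| What is included | Italian total |
|---|---|
| Correction, no dropout | 189 |
| Dropout, no correction (57 × 3 = 171) | 190 by 171/0.9; 189 by 171 × 1.1 |
| Both | 210 by 189/0.9; 208 by 189 × 1.1 |
| Stated, said to include both | 189 |

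Other variants with both elements do not give 189 either: unpooled variance about 212, arcsine about 211, the 50% rate in the larger group 214, one-sided alpha 177.

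**Power if 189 enrol and 10% are lost.** The evaluable number is 189 × 0.9 = 170.1, or 56.7 stapled and 113.4 handsewn.

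- Correction term: c = ½(1/56.7 + 1/113.4) = 0.01323
- Standard error under the null: √(p̄(1 − p̄)(1/56.7 + 1/113.4)) = 0.07667
- Standard error under the alternative: √(0.25/56.7 + 0.1875/113.4) = 0.07786
- Corrected: (0.25 − 0.01323 − 1.960 × 0.07667)/0.07786 = 1.111, power 86.7%
- Uncorrected: (0.25 − 1.960 × 0.07667)/0.07786 = 1.281, power 90.0%

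Exact enumeration of the two binomial distributions:

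| Evaluable (stapled : handsewn) | Corrected chi-squared | Uncorrected chi-squared | Fisher's exact |
|---|---|---|---|
| 57 : 113 | 86.8% | 90.3% | 88.1% |
| 63 : 126 | 90.4% | 92.9% | 91.2% |

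With the corrected test, the stated 90% is reached at 189 evaluable patients and not at 189 enrolled.

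**The case against.** The strongest reply is that the loss depends on the test. The continuity correction appears only as a planning assumption. The section "Statistical analysis" names chi-squared or Fisher's exact test, and "Primary endpoint" names adjusted logistic regression, for which power was not computed. With an uncorrected chi-squared test, power after dropout is still about 90%. This stands as a limit on the size of the problem. It does not rescue the sentence, which names the corrected test and claims 90% for it with dropout included. Fisher's test, at 88.1%, also falls short.

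Second, the effect is small. The shortfall is about three points, type I error is untouched, and 87% is above the 80% accepted for the Dutch trial. That is fair. It is a reason to choose the cheap remedy, not to leave the statement uncorrected.

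Third, more than 189 patients may contribute. If the trial stops after the interim analysis, the plan keeps patients recruited while the six-month follow-up is completed. At steady accrual, 189 over 2.5 years adds 189/2.5 × 0.5, or about 38. That makes 227 enrolled and about 204 evaluable (68 : 136), with exact corrected power near 92%. But the deciding analysis is tied to the first 189, and the text does not say that the later patients enter it.

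Finally, the funding committee's preference explains why the Dutch numbers differ. It does not explain why the Italian number lacks the dropout allowance it is said to contain.

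**Conclusion.** The concern holds. The Italian total of 189 is the continuity-corrected requirement before dropout. It can be reached with dropout only if the correction is removed. With both, as stated, the enrolment would be 210, which is 21 more (11%). With 189 enrolled and 10% lost, power is about 87% for the test the section names, so type II error is about 13% instead of 10%.

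This rests on the stated rates, with 50% in the stapled arm, and on dropout being equal across arms. Reversing the rates raises the requirement slightly (192 before dropout, 214 after) and does not change the conclusion. With an uncorrected chi-squared test the power is about 90%. The trial is not seriously underpowered, but its power statement for the primary comparison is wrong under its own assumptions.

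**What to change.** Keep 189 and correct the statement, for example: 189 patients enrolled, about 170 evaluable after 10% dropout, give 87% power with the continuity-corrected test and 90% with the uncorrected chi-squared test. The cost is one sentence in the protocol and the registry entry, and a slightly lower stated power. No recruitment or analysis changes.

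Saying instead that 189 excludes dropout would make the arithmetic true, but it would leave the 90% unsupported if 10% are in fact lost and enrolment stays at 189. If the sponsor wants 90% with both elements, the first-phase enrolment has to be 210. The abstract and the two-phase Italian total would then change too (210 + 88 = 298 in place of 277), as would the recruitment time.

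### HAND2END's phase-two increment of 88 is added once where End2End's 71 is added per group, so the total of 277 gives about 78–79% power at best for end-to-end versus Kono-S

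*Protocol article*

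**What the plan says.** All the figures are in the protocol article, Sample size calculation.

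- **Phase one, both trials:** 50% versus 25% recurrence, stapled against handsewn, 2:1.
- **Phase one, Italy (HAND2END):** "Assuming a test with continuity correction with 90% power, and an two-sided alpha-level of 0.05"; 63 per surgical arm and 189 in all, described as including 10% dropout.
- **Phase one, Netherlands (End2End):** "assuming a test with continuity correction with 80% power, and a two-sided alpha-level of 0.05"; "a total of 55 patients per arm will be required, for a total enrolment of 165 patients, allowing for a 10% dropout".
- **Phase two, both trials:** only if the interim analysis favours handsewn, end-to-end is compared with Kono-S for a fall in recurrence from 28% to 13%.
- **Phase two, Italy:** "an additional 88 patients need to be included, for a total of 277 in the HAND2END". The next sentence repeats the total and gives 3 or 4 years for 189 or 277 patients.
- **Phase two, Netherlands:** "another 71 patients per group need to be included, leading to a total of 307 patients".

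Neither trial is given a separate power, continuity correction or dropout allowance for phase two. The section closes by attributing slight differences in the Dutch numbers to the funder's review committee.

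**The concern.** The effect is the same in both trials, and so is the two-sided 5% level if it carries over from phase one. The trial with the higher power target should therefore need at least as many patients per arm. Here the order is reversed. The wording shows where the two totals part: the Dutch increment is per group and enters the total twice, while the Italian increment has no such qualifier and enters once.

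End-to-end against Kono-S is one of the two hypotheses in the Abstract, and the article says each trial will be reported separately. A reader who takes the 90% as applying throughout HAND2END would overestimate the chance that its second phase detects a true 15-point difference.

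**Working it through.** **Inputs.** Rates 0.28 and 0.13, so d = 0.15; two-sided alpha 0.05; 1:1 between the handsewn arms. Phase one contributes 63 (Italy) or 55 (Netherlands) per handsewn technique. This assumes that phase-one handsewn patients split evenly and are pooled into phase two, as the Dutch arithmetic implies.

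**Formula.** Pooled-variance sample size per arm, with p̄ = 0.205:

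n = [1.960 × √(2 × 0.205 × 0.795) + z × √(0.28 × 0.72 + 0.13 × 0.87)]² / 0.15²

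The square roots are 0.5709 and 0.5610.

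- 80% power (z = 0.8416): (1.1190 + 0.4721)² / 0.0225 = 112.5, so 113 per arm.
- 90% power (z = 1.2816): (1.1190 + 0.7189)² / 0.0225 = 150.1, so 151 per arm.
- With the Fleiss continuity correction: 125.5 (126) and 163.2 (164).

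**The Dutch figure reproduces.** 113 / 0.9 = 125.6, so 126 per arm; the corrected size without dropout is also 126. Then 126 − 55 = 71 per group, and 165 + 2 × 71 = 307.

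**The Italian figure reproduces only per group.** 151 − 63 = 88 per group, which would make the total 189 + 2 × 88 = 365. The printed total is 189 + 88 = 277, or 63 + 44 = 107 per arm. None of the 90% variants tried gives 88 in all. Even a one-sided uncorrected test needs 123 per arm, which is 60 more per group or 120 in all.

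**Power for 28% versus 13%.** The normal approximation is Φ{[0.15√n − 1.1190] / 0.5610}. For n = 107 it is Φ(0.771) = 78.0%. Exact binomial power of the chi-squared test is alongside.

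| Evaluable per arm | How it arises | Normal approx. | Exact, uncorrected | Exact, corrected |
|---|---|---|---|---|
| 107 | 277, no dropout | 78.0% | 78.8% | 73.4% |
| 96 | 277, 10% dropout (107 × 0.9 = 96.3) | 73.4% | 74.4% | 67.8% |
| 151 | 365, no dropout | 90.2% | 90.7% | 88.1% |
| 136 | 365, 10% dropout (151 × 0.9 = 135.9) | 86.9% | 87.7% | 84.0% |

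**Timeline.** 189 patients in 2.5 years is 75.6 a year. At that rate 277 takes 3.7 years and 365 takes 4.8 years, each plus half a year of follow-up.

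**Sensitivity notes only.** (a) The rates 28% and 13% average 20.5%, while phase one assumes 25% for the combined handsewn arm. With 32.5% versus 17.5%, which average 25%, exact uncorrected power is 68% at 96 per arm and 75% at 113. (b) End2End at 113 evaluable per arm has about 80–81% power uncorrected and 76% corrected. Neither note is part of the inconsistency.

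**The case against.** - **No phase-two power target is stated.** This stands. The 90% belongs to the 50% versus 25% contrast. A reader might infer that the protocol promises 90% for end-to-end versus Kono-S and breaks the promise; the text does not go that far. What remains is that no lower target is declared, and that 277 misses 90% if the figure carries over.
- **Setting 74% against 90% is not like for like.** This also stands. The benchmark of 151 has no dropout allowance, and on that basis 107 per arm gives 78–79%. The 74% applies only after 10% dropout.
- **The match 151 − 63 = 88 is suggestive, not proof.** The 63 is described as an enrolled number that already allows for dropout, whereas 151 is an evaluable number without correction. The Dutch 126 needs either the correction or the dropout allowance. The origin of the 88 is therefore a well-supported inference. The inconsistency does not depend on it.
- **277 fits the stated duration.** It appears twice and agrees with about 4 years; 365 does not. So 365 cannot be taken as the intended total, and adopting it would be more than a wording change.
- **The funder's review explains the difference.** It does not. That remark concerns slight differences in the Dutch numbers. It does not account for counting one increment once and the other twice, or for the reversed order of the sizes.
- **A null result at 277 would be read as equivalence.** A reader might fear this, but the article calls both trials superiority trials and plans no equivalence claim.

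**Conclusion.** The passage is inconsistent as written. For one and the same contrast, 88 is counted once and 71 twice, so HAND2END has 107 patients per handsewn arm against 126 in End2End, despite its higher phase-one power. At 277, power for 28% versus 13% is about 78–79% with everyone evaluable (73% corrected) and about 74% after 10% dropout (68% corrected). That is short of 90% on every basis tried.

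The inconsistency and the shortfall from 90% are firm. That 88 was meant per group is likely but not established. The power figures rest on an even split of phase-one handsewn patients, their pooling into phase two, 1:1 allocation and a two-sided 5% level. The point concerns only the conditional second phase. It does not touch the handsewn-versus-stapled comparison or its 189 patients.

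**What to change.** Reconcile the Italian sentence in one of two ways.

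1. **Keep 277 and state its power.** Say that it gives 107 per handsewn arm, with about 78–79% power for 28% versus 13% with no dropout and about 74% after 10% dropout, for an uncorrected two-sided 5% test (73% and 68% with continuity correction). This costs wording only, although the stated figure is less favourable.
2. **If 88 per group was meant, correct the total to 365.** Revise the 3-or-4-year duration as well, and state that 365 gives about 90% only with no dropout and no correction; after 10% dropout it gives about 88% uncorrected and 84% corrected. This costs 88 more patients (365 − 277) and about 1.2 more years at the planned accrual (88 / 75.6).

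In either case, state the phase-two power, continuity correction and dropout basis for both trials, and whether phase-one handsewn patients are pooled into the phase-two comparison.
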